**Figure 1 figure1:**
[figure not shown]
The helpful activities before it is time to sleep study design using Williams Latin square randomization design.

### Ethical Considerations

The HABITS study was approved by the University of Otago Health Ethics Committee (H23/039) and is registered with the Australian New Zealand Clinical Trials Registry (ACTRN12624000206527; www.anzctr.org.au). Written informed consent will be obtained from adult and child participants before the first appointment. We also follow ethical frameworks for the use of wearable cameras in research [59]. In brief, this includes discussing with participants and families about privacy considerations (eg, everyone in the household needs to be happy to be recorded, remove the camera when toileting or someone asks), families get to view the footage before the research team does and can delete any footage without explanation, and that footage is deleted from cameras as soon as it is uploaded to our high-capacity secure storage system.

### Sample Size

To detect a difference of 15 minutes (assuming within-person SD of 35 minutes) in TST [60], with 90% power at a .05 α level, a sample size of 60 participants would be required. We will recruit 72 children, allowing for 20% nonadherence, dropout, or incomplete data.

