### Statistical Analyses

Siblings in the same family may wish to participate, and they would be convenient participants, given their familiarity with the intensive intervention protocols. However, siblings represent family clustering that must be statistically accounted for. We examined the intraclass correlation coefficient (ICC) for families in our recent observational repeated-measures study of screen use and sleep in teens [73], which was low (ICC=0.005). Using this ICC and an average family cluster size of 2, the design effect is 1.005 [74], which has a negligible effect on the required sample size (60*1.005=60.3). Therefore, siblings may be recruited but will be assessed at different times throughout the year, will be individually randomized, and will contribute to no more than half the sample (ie, n=36 participants must not have siblings in the study).

Primary statistical analyses will be undertaken using data from adherent days; secondary analyses will use all data. Mixed effects regression models with a random effect for participants nested within a family cluster will be used to estimate mean differences, 95% CI, and *P* values for conditions 2, 3, and 4 compared with condition 1. Residuals will be plotted and visually assessed for homoskedasticity and normality. Adjustments for within-person confounding (eg, lunar phases) will be undertaken as sensitivity analyses. Results will be reported in line with the CONSORT (Consolidated Standards of Reporting Trials) statement extension to crossover trials. Descriptive analyses will also be undertaken to explore participants’ experiences with the interventions as well as their adherence. Relationships between sleep and quality of life measures will be assessed using repeated measures mixed effects analyses.

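### Recruiting 72 children covers a loss of 16.7%, not the stated 20%: a 20% loss leaves 57 or 58 children against the 60 required, a shortfall of about one percentage point of power

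*Protocol article*

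**What the plan says.** The Sample Size section of the protocol article gives the whole calculation in two sentences. The target is set out as "To detect a difference of 15 minutes (assuming within-person SD of 35 minutes) in TST", and the result as "with 90% power at a .05 α level, a sample size of 60 participants would be required". The recruitment figure follows: "We will recruit 72 children, allowing for 20% nonadherence, dropout, or incomplete data". The abstract repeats 72.

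The formula that leads from 60 to 72 is not printed, and the base of the 20% is not stated. No other section explains 72 differently. The Statistical Analyses section bases the primary analysis on adherent days and uses all data in secondary analyses.

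**The concern.** Nonadherence, dropout and incomplete data arise among children who have been recruited, so the natural base for the 20% is 72. Read that way, the allowance does not leave the 60 children that the same section says are needed.

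At stake is the accuracy of a stated design property. The Discussion lists adequate power among the trial's strengths and expects that the three behaviours may have only a limited effect on sleep. If the results are close to null, readers will look at how much loss the stated power can absorb. Nonadherence also removes data directly from the primary analysis, so the allowance is not a formality here.

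**Working it through.** **Inputs, all from the Sample Size section:** difference δ = 15 minutes; SD = 35 minutes; power 90%; α = 0.05 (sidedness is not stated; two-sided is assumed); required n = 60; recruited n = 72; loss allowance 20%.

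**Step 1. Reproduce the 60.** Take 35 minutes as the SD of the paired difference between two conditions.
- Normal approximation: n = (1.960 + 1.282)² × 35² / 15² = 57.2, rounded up to 58.
- Paired t-test: power comes from the noncentral t distribution with n − 1 degrees of freedom and noncentrality 15√n / 35. At n = 60 the noncentrality is 15 × √60 / 35 = 3.32 and the power is 90.4%. At n = 59 it is 89.9%.

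So 60 is the smallest number that reaches 90%. The plan's figure is reproduced, and it carries almost no slack.

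**Step 2. From 60 to the recruitment target.**
- To keep n after losing a share d of those recruited: n / (1 − d) = 60 / 0.8 = 75.
- As a mark-up on the required number: n × (1 + d) = 60 × 1.2 = 72.

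Only the second gives the stated 72.

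**Step 3. What 72 provides.**
- Children left after a 20% loss: 72 × 0.8 = 57.6, so 57 or 58.
- Loss that leaves exactly 60: (72 − 60) / 72 = 12/72 = 16.7%.

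**Step 4. Cost in power**, by the same paired t-test as in step 1, with each lost child contributing nothing:

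| Analysable children | Power |
|---|---|
| 60 | 90.4% |
| 59 | 89.9% |
| 58 | 89.4% |
| 57 | 88.9% |

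Against the stated 90%, the shortfall is 90 − 89.4 = 0.6 to 90 − 88.9 = 1.1 percentage points. Against the 90.4% that 60 children give, it is 1.0 to 1.5 points.

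**The case against.** **The 20% may be meant as a share of 60.** The text does not name the base, and 20% added to 60 is exactly 72, so this may be loose wording and not a miscalculation. That stands as an account of how 72 arose; the mark-up is an inference. It does not rescue the sentence, because a reader will take an allowance of "allowing for 20% nonadherence, dropout, or incomplete data" to mean that one recruited child in five can be lost.

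**A lost child is rarely lost entirely.** The design plans three nights per child per condition, and the analysis is a mixed model on adherent days. Nonadherence and incomplete data will often remove single nights or one condition and leave the rest of the child's data in. This stands. It makes the power figures above a simplified case in which all the loss falls on whole children.

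**A reader might infer that 72 cannot give 90% power with a 20% loss.** The documents do not support a claim that strong. Suppose that 35 minutes is the within-person SD of a single night, that three nights per condition are averaged, that nights are independent, and that the effect of condition does not vary between children. The SD of the difference is then 35 × √(2/3) = 28.6 minutes, and 57 children give about 97% power. That reading does not reproduce 60, so it is not the plan's own calculation, but it shows that the shortfall depends on what the 35 minutes describes. That ambiguity is a separate question. It should not be used to make this point look larger or smaller.

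**A reader might also want the sibling adjustment carried into the target.** The Statistical Analyses section discloses the adjustment and says that it "has a negligible effect on the required sample size (60*1.005=60.3"). Leaving out 0.3 of a child is an open choice. The unrounded requirement from step 1 is also about 59.2, and 59.2 × 1.005 = 59.5 still rounds up to 60.

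**Conclusion.** The point holds, and it is minor. If the 20% is a share of recruited children, the stated 60, 72 and 20% are inconsistent: 72 tolerates a 16.7% loss, and a 20% loss leaves 57 or 58 children. Power is then about 89% (88.9% to 89.4%) against the stated 90%, a shortfall of about one percentage point.

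The power figures rest on three assumptions: 35 minutes is the SD of the paired difference (the reading that reproduces 60), the test is two-sided at 5%, and lost children contribute no data. The head count (57.6, 75 and 16.7%) needs none of these.

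A reader might conclude that the trial is underpowered. This discrepancy does not show that: it changes no design feature, analysis or conclusion.

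**What to change.** Reword the sentence in the Sample Size section in one of two ways:

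- State that 72 allows for a loss of 16.7%, that is, 12 of the 72 children recruited.
- Keep 20%, name recruited children as its base, and state that the 57 to 58 analysable children then left give about 89% power to detect 15 minutes, with 35 minutes as the SD of the paired difference.

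Either way the cost is one sentence and a slightly less favourable stated figure. No extra enrolment is needed, and the design and analysis stay as they are.

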### Recruitment and Eligibility

#### Overview

Recruitment will take place through social media and community networks. Interested families will complete an eligibility screening questionnaire online (assessing whether their child has, or previously had, a sleep disorder, any medications that may impact sleep, and ability to undertake physical activity), which they will access through local Facebook (Meta) pages or email from the researchers. Children will be eligible to participate if they are 10-15 years old and live in the Dunedin area. Children will be excluded if they have been diagnosed with a sleep disorder or issue or are on medication that may affect sleep. Children who are not eligible will be sent a standardized text or email by their caregiver. We aim to recruit a sample that is broadly representative of the New Zealand population [61].

Before attending the baseline appointment, potentially eligible participants will be asked to select 3 consecutive nights in the week that would work best for them to complete the intervention (eg, Mondays, Tuesdays, and Wednesdays). These days will be classified as days 5-7 for participant baseline (week 1) and intervention (weeks 2-5) weeks. The researchers will then book their baseline appointment on day 1 of the baseline week.

#### Baseline (Week 1)

At the baseline appointment, researchers will explain the study protocol to potential participants and their caregivers (mainly parents), with opportunities for questions throughout. If the child and their caregiver indicate that they would like to be involved, they will be given a paper version of the assent (child) and consent (caregiver) form to sign. Once consent and assent are signed, caregivers will complete an online demographics questionnaire assessing the child’s date of birth, household address, and ethnicity. Weight (using Tanita electronic scales HD351) and height (using Wedderburn Portable Height Rod, WS-HRP) will be measured by trained researchers using standard procedures [62].

Participants will be given an accelerometer (AX3 [Axivity]) to wear on their nondominant wrist for 7 nights, 24 hours per day, to measure usual sleep (more details are discussed in the *Intervention Adherence* section). To determine usual bedtime practices in terms of screen time, physical activity, and food consumption, participants will be asked to wear a wearable video camera from 90 minutes before bedtime until bedtime on their 3 “intervention” nights (more details are discussed in the *Intervention Adherence* section). A second stationary camera in the child’s bedroom will face the bed and allow researchers to measure in-bed electronic use or eating, and to measure when the participants attempt sleep (shut-eye time; more details are discussed in the *Sleep* section). Participants will be asked not to change their behavior during the baseline week. Information from the cameras will also be used to give researchers insight into how the participants might be able to adapt their nighttime behavior to complete the intervention weeks. Researchers will talk to participants (and families) at the baseline visit about their usual eating, physical activity, and screen time habits to help develop personalized suggestions for completing the intervention weeks.

### Randomization

#### Overview

Once the baseline appointment is completed, participants will be randomized using the REDCap (Research Electronic Data Capture; Vanderbilt University) randomization module [63] to one of 4 intervention group orders using a computer-generated sequence, stratified by age (from 10 to less than 13 years or from 13 to 15 years), with random block sizes of 4 or 8. The 4 group orders are from a Williams Latin square balanced for first-order carryover effects. Usual bedtimes will be discussed with families, based on camera footage from baseline. While bedtime for each night of intervention (ie, nights 5-7 of each intervention week) can be different, each day of the week must be consistent between all 4 intervention weeks.

#### Intervention (Weeks 2-5)

At the start of each intervention week, a trained researcher will visit the participants at home to inform them which intervention (screens, physical activity, food, or none week) they are completing that week. The researchers will discuss potential ideas with the participants based on their baseline week information on how to adhere to that week’s protocol.

As the participants will potentially be asked to do less (ie, not use screens) or more (ie, eat dinner close to bedtime) than they usually would do before bed, they will be given ideas for filling in the time while avoiding their usual prebedtime activities. For example, researchers will suggest games or reading for the nonscreen weeks and discuss rescheduling of the family dinner during the food week. These strategies will be put in place specifically to encourage adherence, so that we can determine the true effect of each prebed behavior on sleep. During the physical activity week, we will give each participant a Fitbit Inspire 3 (Google) to measure their heart rate while exercising. Participants will be able to see their heart rate and asked to aim for a target heart rate of 65% of their maximum ([208-0.7*age]*0.65) [64] during the 30 minutes of activity. Participants and their caregivers will receive regular text reminders, letting them know what intervention to complete each night, and when to turn the cameras on.

### Intervention Adherence

Objective and subjective measures will be used to assess adherence. On days 5-7 of each intervention week, participants will wear a PatrolEyes Max (StuntCams) camera on a chest harness from 90 minutes before bedtime until bedtime. These cameras (weighing 160 g and having dimensions 79×57×27 mm) provide time-stamped footage, face outwards, record audio and video (including overnight use through infrared), and quantify when and how much screen use has occurred [65]. We will also be able to determine when and what food or beverages were consumed, supplemented with a brief questionnaire (text message) on mornings 6, 7, and 8, asking them whether they consumed any food or drinks in the hour before bed last night, as well as any caffeine intake. We will use the wearable cameras to code for moderate-to-vigorous physical activity (Compendium of Physical Activity metabolic equivalent values >4 [66]) using a reliable video coding protocol that codes free-living physical activity behavior, supplemented with information from heart rate monitors and accelerometers. Since the wearable cameras can be removed before bedtime (eg, bathing), a second stationary camera will be set up in the participant’s bedroom 10 minutes before bedtime. This “back-up” camera would detect any time-stamp missing from the wearable camera (as long as the participant is in their bedroom) and is also used to assess some aspects of sleep (more details are discussed in the *Sleep* section). It will not be possible to blind coders (as they are looking for specific behaviors) or participants (as they know what behaviors they need to do), but statistical analysis will be undertaken blinded to the intervention order.

The following predefined cut-offs will be used to classify participants as “adherent” for the per-protocol analysis (ie, those who followed the HABITS protocol):

Condition A: children use screens and engage in physical activity for less than 5 minutes and do not consume any food or beverages other than water in the hour before bed.Condition B: children spend at least 30 minutes on screens in the hour before bed (and engage in physical activity for less than 5 minutes and do not consume any food or beverages other than water).Condition C: children spend at least 30 minutes being physically active (light, moderate, or vigorous activity) in the hour before bed (and use screens for less than 5 minutes and do not consume any food or beverages other than water).Condition D: children consume their dinner meal in the hour before bed (and use screens and engage in physical activity for less than 5 minutes).

Video data will be examined to describe how children are spending this time, based on a reliable (κ≥0.8) coding schedule previously developed by our team [65].

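### Condition D's adherence cut-off sets no drink or caffeine limit, so a last-hour caffeinated drink keeps a D night in the primary analysis but removes an A, B or C night

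*Protocol article*

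**What the plan says.** The cut-offs are in the Intervention Adherence section of the protocol article.

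- Condition A (comparator): screens and activity each under 5 minutes, and children "do not consume any food or beverages other than water in the hour before bed".
- Condition B: "children spend at least 30 minutes on screens in the hour before bed (and engage in physical activity for less than 5 minutes", with the same water-only limit.
- Condition C: at least 30 minutes of activity, and children "use screens for less than 5 minutes and do not consume any food or beverages other than water".
- Condition D: "children consume their dinner meal in the hour before bed (and use screens and engage in physical activity for less than 5 minutes". There is no clause on drinks.

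The section introduces these rules as follows: "The following predefined cut-offs will be used to classify participants as “adherent” for the per-protocol analysis". Statistical Analyses then gives them their weight: "Primary statistical analyses will be undertaken using data from adherent days; secondary analyses will use all data".

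On caffeine, Intervention Adherence describes a questionnaire sent by text (mornings 6, 7 and 8) with this content: "asking them whether they consumed any food or drinks in the hour before bed last night, as well as any caffeine intake". The chest camera, worn from 90 minutes before bed, also shows what is drunk and when. Neither source of caffeine information enters a cut-off. The planned confounder work is "Adjustments for within-person confounding (eg, lunar phases) will be undertaken as sensitivity analyses"; caffeine is not named there.

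**The concern.** The cut-offs are built so that each condition differs from A in one behaviour. D has to lift the ban on food, but the ban on drinks is lifted with it. Nothing replaces it for the kind of drink most likely to affect sleep in its own right.

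The primary aim is the effect of a meal on TST. If some adherent D nights include last-hour caffeine and no adherent A night can, part of any D minus A difference may belong to the drink. The trial is meant to inform sleep guidelines, so an effect of caffeine could be credited to late eating. Because caffeine is recorded but given no stated use, its handling could also end up being chosen after the data are seen, and that choice bears mainly on one primary contrast.

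**Working it through.** **1. One drink traced through the four rules**

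| Drink | A | B | C | D |
|---|---|---|---|---|
| Cola 30 min before bed | not adherent | not adherent | not adherent | adherent |
| Water 30 min before bed | adherent | adherent | adherent | adherent |
| Cola 75 min before bed | adherent | adherent | adherent | adherent |

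Each cell assumes that the other requirements of the condition are met. Row 1 is the asymmetry. Row 3 shows its limit: the water-only rule covers only the last hour, so earlier caffeine is allowed everywhere.

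**2. Route to the primary result.** Statistical Analyses bases the primary analysis on adherent days, so row 1 decides which nights enter D minus A. The all-data analysis does not isolate the problem either, because caffeine nights stay in it for every condition.

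**3. The yardstick.** Sample Size plans for a 15-minute difference with SD 35, 90% power and alpha .05 (taken as two-sided), and gives 60. Taking 35 as the SD of the within-person difference:

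- Normal approximation: (1.960 + 1.282)² × 35² / 15² = 57.2, so 58.
- Paired t: power 0.899 at n = 59 and 0.904 at n = 60, so 60.

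The figure reproduces. The point does not rest on it; 15 minutes serves only as a scale.

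**4. Possible shift, if A nights carry no caffeine.** Let p be the share of adherent D nights with last-hour caffeine and e the loss of TST on such a night. Neither is in the documents; both are assumptions. The shift in D minus A is p × e.

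| p | e (min) | p × e (min) | Share of 15 min |
|---|---|---|---|
| 5% | 10 | 0.5 | 3% |
| 10% | 20 | 2 | 13% |
| 20% | 30 | 6 | 40% |
| 40% | 30 | 12 | 80% |

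**5. Possible shift, if the drink moves with dinner.** A child who always has cola with dinner has it late in D and earlier in A. If the earlier drink costs f minutes of TST, the shift for such nights is p × (e − f). With p = 10%, e = 20 and an assumed f = 10, it is 10% × (20 − 10) = 1 minute, half of the 2 minutes in step 4. With f = e it is zero. Step 4 therefore overstates the shift to the extent that A nights carry earlier caffeine.

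**The case against.** The strongest reply is that the asymmetry is mostly the intervention itself. A, B and C prohibit food and drink in one clause, and D must lift that clause for a meal to be eaten. A drink with dinner can fairly be called part of dinner, and the Discussion accepts variation in how families interpret the evening meal as appropriate to a pragmatic trial. This stands for drinks in general, and the fix leaves them alone. It is weaker for caffeine: the primary analysis is confined to nights that meet tight single-behaviour limits, and the protocol thought caffeine worth asking about.

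A second reply is that handling a recorded covariate belongs in the analysis plan, and that lunar phase is only an example of the planned adjustments. For the adjustment this is fair. It does not cover the cut-offs, which the article states for all four conditions and which treat the same drink differently.

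A reader might infer more than the text supports, in three ways:

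- *That caffeinated nights never count in A, or that D minus A compares meal plus caffeine with neither.* This is true only of the last hour. Caffeine taken earlier leaves an A night adherent, so for some children the contrast is in timing, not presence versus absence.
- *That the estimate is biased, and by a known amount towards harm.* The rule permits mixing; nothing shows how often it happens among these children. The direction rests on caffeine shortening TST, which is also an assumption.
- *That a clause in D alone settles it.* Removing D nights with caffeine at a late dinner while keeping A nights with caffeine at an earlier one could tilt the contrast the other way.

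**Conclusion.** The point holds in limited form. D's cut-off has no drink or caffeine condition, A, B and C allow only water, and the difference reaches the primary D minus A contrast because that contrast uses adherent days. The contrast can therefore mix the meal with last-hour caffeine.

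The size cannot be settled from the documents. Under the assumptions shown it runs from 0.5 to 12 minutes, from trivial to most of the target difference, and it shrinks towards zero where the same child has caffeine earlier on A nights. It may well be negligible. The B and C contrasts with A are not affected, since those three conditions share the same water-only rule. The sample size is not affected either. The change is worth making because it is cheap and has to be fixed before the data are examined.

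**What to change.** Before analysis:

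1. Add to the condition D cut-off that a night with a caffeinated drink in the last hour, seen on camera or reported in the morning text, is non-adherent. Other drinks remain allowed as part of the meal. Last-hour caffeine is then treated alike in all four conditions.
2. Add a named sensitivity analysis that excludes, or adjusts for, nights with any recorded caffeine intake by the same rule in A, B, C and D. Run it in both the adherent-day and the all-data analyses. This covers earlier caffeine, which step 1 does not touch.
3. State whether the morning caffeine question refers to the last hour or to the whole evening. The wording can be read either way, and the camera covers only the final 90 minutes, so step 2 depends on the answer.

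The cost is one clause, one sensitivity analysis on data already being collected, and some lost nights. With 72 children and 3 nights there are at most 72 × 3 = 216 D nights. Losing 5% would be about 11 and losing 20% about 43. If few are lost, the primary analysis barely changes; if many are, the mixing was common enough to need removing.
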